## Aims

### Primary Aim

The aim of this study is to develop and validate an individual-based model that can be used to predict the communication impairment of children with BCP and PWMLs at school entry based on advanced brain MRI at an early age (before 2 years).

### Secondary Aims

(1)To establish a practical method for multivariate lesion- and connectome-based approaches of children with BCP and PWMLs.(2)To identify injuries to cortical regions and connectomes associated with communication impairment in children with BCP with PWMLs.

## Materials and Methods

### Study Design

This study will be implemented as a multicenter prospective cohort study at four centers. This study has been registered with the Chinese Clinical Trial Registry (ChiCTR2100049497) and will be reported in accordance with the Standard Protocol Items: Recommendations for clinical Trials (SPIRIT) (Chan et al., 2013).

#### Study Setting

The study will take place at the Affiliated Hospital of Zunyi Medical University ([name]), the First Affiliated Hospital of Xi’an Jiaotong University ([name]), the First Affiliated Hospital of Henan University of Chinese Medicine ([name]), and Chongqing University Central Hospital ([name]). The study will begin in December 2021 and is expected to be completed in June 2025.

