#### Inclusion Criteria

Children meeting the following criteria will be considered for enrollment in this study: (I) confirmed diagnosis of BCP by pediatric neurologists (Novak et al., 2017), (II) age 6 months to 2 years at the time of recruitment, (III) PWMLs as described on the MRI imaging report, and (IV) willingness by participants and parents to participate in the study.

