### Study Procedures

The study procedures are shown in Figure 1. Following the inclusion and exclusion criteria, eligible participants (children with BCP and PWMLs) will be entered from corrected ages of 6 to 24 months. Participants will be assessed for diagnostic criteria, differential diagnosis and comorbidities by a pediatrician or child neurologist. The participants will undergo at least 1 advance brain MRI examination according to a standardized protocol. A variety of clinical data and data pertaining to socioeconomic status will be collected. Neurobehavioral development will be assessed by experienced physiotherapists blinded to the MRI findings and related medical information (such as other examination results relevant to the content of the current assessment) at each center.

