**FIGURE 1 F1:**
[figure not shown]
Flow chart of the study protocol. BCP, Bilateral Cerebral Palsy; PWML, Periventricular White Matter Lesion; MRI, Magnetic Resonance Imaging; GMFM, Gross Motor Function Measure; GMFCS, Gross Motor Function Classification System; MACS, Manual Ability Classification System; VSS, Viking Speech Scale; CBBS-DP, Communication and Symbolic Behavior Scales Developmental Profile; FCCS, Function Communication Classification System; PPTV-R, Peabody Picture Vocabulary Test-Revised; WPPSI-IV, Wechsler Preschool and Primary Scale of Intelligence.

At the age of 48–60 months, the participants will be invited back to the hospital for a follow-up assessment. Experienced speech and language therapists (SLTs) blinded to the medical history will assess each child’s communication ability using multiple classification systems and scales. The primary outcome measure for this study is the communication function classification system (CFCS) rating. Secondary outcome measures include ratings from the Functional Communication Classification System (FCCS), Viking Speech Scale (VSS), Peabody Picture Vocabulary Test-Revised (PPTV-R), verb comprehension subtest of the Wechsler Preschool and Primary Scale of Intelligence (WPPSI-IV), and CSBS-DP Infant-Toddler Checklist. The questionnaire data (CSBS-DP) will be collected by trained researchers during a telephone survey for participants who are reluctant to return to the hospital for follow-up. Other measures, such as Gross Motor Function Classification (GMFCS), Manual Ability Classification System (MACS), WPPSI-IV, and advanced brain imaging, will also be used to evaluate the development of participants during the follow-up assessment.

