Images from four sites (four hospitals) will be randomly partitioned into four equal portions. Approximately three-quarters of these images will be used as a “training cohort,” and the remaining one-quarter of these images will be used as a “test cohort.” In the “training cohort,” the proportion of lesioned voxels in the ROI and the links of the connectome matrix that are not shown difference between absence of communication impairment group and communication impairment group will be excluded, where the significance level is defined as *P* < 0.05 without multiple comparison correction in the two-sample test. The selected features will be used to define models predicting presence or absence of communication impairment in children with BCP. For each prediction model, 10-fold cross-validation (CV) will be used to evaluate the performance. This means that the “training cohort” will be divided into a training (nine folds) and a validation dataset (one fold), leaving 9 of 10 participants in the training dataset and the remaining participants in the testing dataset. For the training cohort, the various hyperparameters within each algorithm will be used to determine the prediction model. Then, the model will be applied to the validation dataset to predict children with the presence or absence of communication impairment (predicted label). The same procedure will be repeated with each of the one-fold participants or the left-out participants in the leave-one-out procedure, serving as the validation dataset for 10 iterations. Thus, each subject will receive a predicted label, and the accuracy of predictive model will be evaluate by comparing predicted labels to true labels of BCP children. The CV step will be repeated 100 times with random cohort designation to select the model with the best prediction accuracy. The whole “training cohort” will be reused in its entirety to retrain the model based on the classification algorithm and hyperparameters of the prior selected model. Then, the retrained model will be used to evaluate the “test cohort,” and the communication performance of every subject of the “test cohort” will be predicted by the model. The final accuracy of the prediction model will be defined by comparing predicted labels to true labels of BCP children in the “test cohort,” The Receiver Operating Characteristic (ROC) curve and the area under curve (AUC) will be calculated to evaluate the predictive ability of built models. A two-sided Hotelling-Williams test (Steiger, 1980) will be used to determine whether the multimodality prediction model is more accurate than any of the single-modality prediction models. *P* values < 0.05 will be considered indicative of statistically significant differences across models. Given the possible effects of age on imaging measures, the “test cohort” will be divided into three groups: younger (6–12 months), middle-aged (12–18 months), and elderly (18–24 months years), according to their age at MRI scan. The optimal model will be applied to all subgroups to exam whether the prediction accuracy changes with age at MRI scan.

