### Trial Status

This trial is currently recruiting participants.

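### The expected completion date of June 2025 does not fit prospective entry at 6–24 months with the primary outcome assessed at 48–60 months

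*Protocol article*

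**What the plan says.** All places are in the protocol article.

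- Study Design: "This study will be implemented as a multicenter prospective cohort study at four centers".
- Study Setting: "The study will begin in December 2021 and is expected to be completed in June 2025".
- Inclusion Criteria: "age 6 months to 2 years at the time of recruitment". Study Procedures adds that the ages are corrected: children "will be entered from corrected ages of 6 to 24 months".
- Study Procedures, below Figure 1: "At the age of 48–60 months, the participants will be invited back to the hospital for a follow-up assessment". The age is not labelled as corrected or chronological. The same paragraph states: "The primary outcome measure for this study is the communication function classification system (CFCS) rating".
- Trial Status: "This trial is currently recruiting participants". No recruitment period is given.
- Sample Size: 143 children are required, raised to 178 for a dropout rate of at most 20%.
- Development and Validation of Prediction Models: the test cohort, about a quarter of the images, is split into "younger (6–12 months), middle-aged (12–18 months), and elderly (18–24 months years), according to their age at MRI scan" to see whether accuracy changes with age.

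The telephone option in Study Procedures covers only the CSBS-DP questionnaire, so it does not supply a CFCS rating.

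**The concern.** The start date, end date, entry ages and outcome age are all stated, and they do not fit together unless recruitment is very short. A child recruited at the bottom of the age range needs the whole study period just to become old enough for the outcome visit.

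If data collection stopped in June 2025, the children without a primary outcome would be those who were youngest at MRI or recruited late. The loss would therefore depend on age at MRI, the factor the subgroup analysis is meant to examine, and it would fall hardest on the children for whom early prediction is the aim. It would also come on top of the 20% allowance, which the article bases on previous follow-up experience and which makes no provision for children too young at closure. Rating such children before 48 months would depart from the stated outcome age.

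**Working it through.** **The plan's own figure.** Overall F test of R² with 6 predictors, f² = 0.10, α = 0.05, noncentrality f²·N, degrees of freedom 6 and N − 7. N = 143 is the smallest N with power of at least 0.80 (0.801), so the stated figure reproduces. 143 / 0.8 = 178.75, which rounds up to 179 against the stated 178; the difference is immaterial. Conversely, 178 × 0.8 = 142.4.

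**Length of the study, W.** 1 December 2021 to 1 June 2025 is 42 months; to 30 June it is about 43.

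**Condition for one child.** A child entering at age *a* months, *t* months after the start, reaches 48 months in time only if t + (48 − a) ≤ W, that is t ≤ a − 6 for W = 42 or t ≤ a − 5 for W = 43.

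| Age at entry | Follow-up needed to 48 months | Latest entry, W = 42 | Latest entry, W = 43 |
|---|---|---|---|
| 6 months | 42 months | December 2021 | January 2022 |
| 12 months | 36 months | June 2022 | July 2022 |
| 18 months | 30 months | December 2022 | January 2023 |
| 24 months | 24 months | June 2023 | July 2023 |

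This table rests on the article's figures alone.

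**Share of children who fit.** This needs two assumptions the article does not supply: even accrual over R months, and entry age uniform over 6–24 months. For R up to 18 months the share is

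- W = 42: 1 − R/36
- W = 43: 1 − (R − 1)²/(36R)

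For R = 12 these give 1 − 12/36 = 0.667 and 1 − 121/432 = 0.720. Evaluable children are 178 × 0.8 × share; for R = 12, 142.4 × 0.667 ≈ 95 and 142.4 × 0.720 ≈ 103. Power uses the plan's own formula. Each range runs from W = 42 to W = 43.

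| Accrual R | Reach 48 months, all | Reach 48 months, 6–12-month band | Evaluable of 178 after 20% dropout | Power |
|---|---|---|---|---|
| 3 months | 92–96% | 75–89% | 131–137 | 0.75–0.78 |
| 6 months | 83–88% | 50–65% | 119–126 | 0.70–0.73 |
| 12 months | 67–72% | 25–33% | 95–103 | 0.58–0.62 |
| 18 months | 50–55% | 17–22% | 71–79 | 0.43–0.48 |

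Without any dropout, 12 months of accrual would leave 119–128 children, still below 143.

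**Youngest test subgroup, 12 months of accrual.** A third of 178 is 59.3 children. After 20% dropout and the one-quarter split, 59.3 × 0.8 × 0.25 ≈ 12 would be expected if all reached 48 months. With 25–33% reaching it, about 3 to 4 remain. All children in the 18–24-month band would still reach 48 months.

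**Corrected or chronological age.** If the outcome age is chronological, preterm children gain some time. With an assumed 3 months for every child, the share missed is 15–19% for R = 12 and 30–35% for R = 18. For W = 42 that leaves about 142.4 × 0.8125 = 116 and 142.4 × 0.653 = 93 evaluable children.

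In other respects the calculation favours the plan: it takes the lowest outcome age, assumes attendance on the day the child turns 48 months, and leaves no time for analysis.

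**The case against.** The strongest reply is that June 2025 is only an expected date. The outcome visit is set by the child's age, and nothing in the article says that follow-up stops then. A child under 48 months at that time may simply be followed for longer, in which case no outcome is lost, power is unaffected and only the forecast date is wrong. A reader might infer that primary outcomes will be missing by design; the article does not support that, because the loss arises only if the date is enforced as a data cut-off.

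A reader might also infer that a large share of children certainly cannot be assessed. That is not established either. Accrual length and entry-age mix are not given, and an article may leave the recruitment period to the full protocol. The statement that recruitment is under way carries no date. With 3 months of accrual only 4–8% of children would miss 48 months, and if everyone entered in the first month virtually all would fit. An older entry mix, or an outcome age counted chronologically, would reduce the loss further.

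These points stand, and they make the size conditional. They do not remove the inconsistency: the article leaves the full 6–24-month entry range open with no stated closing point for recruitment, and the end date cannot accommodate that.

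**Conclusion.** The stated completion date is incompatible with the stated entry and outcome ages unless enrolment of the youngest children ends almost at once and all enrolment ends by about mid-2023. That much follows from the article's own figures.

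The tabulated losses rest on even accrual and uniform entry age, and the counts and power also on the full 20% dropout. Under these assumptions the evaluable number is below 143 in every accrual scenario shown, and the shortfall is modest at 3 months and severe at 12 or more. Harm to the analysis (outcomes missing by age at MRI, a depleted youngest subgroup, less than the stated 80% power) is conditional on a hard stop in June 2025. If follow-up runs on, the error is confined to the date. The document should be corrected in either case, because the amendment is cheap and selective loss of outcomes could not be repaired at analysis.

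**What to change.** Reconcile Study Setting with Inclusion Criteria and Study Procedures:

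1. State the recruitment period, and restate completion as last enrolment plus up to 42 months (48 − 6), plus time for analysis. For illustration, if recruitment closed in December 2022, the last 6-month-old would turn 48 months in June 2026. The point is that every enrolled child is assessed at 48–60 months before the database closes.
2. Say whether the 48–60 months are corrected or chronological age.
3. State that CFCS ratings taken before 48 months are not used as the primary outcome.

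The cost is an amendment of dates in the protocol and registry, a later completion date and longer follow-up. No extra children are needed, and the sample-size calculation is unchanged.

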#### Ethics and Dissemination

All participating centers approved this study protocol. Full ethics committee approval was obtained from the Institutional Review Board of The Affiliated Hospital of Zunyi Medical University (KLL-2021-108). A signed, informed consent form will be obtained from the legal parents/guardians of each participant. Participating subjects will receive a summary of the results, including clinical phenotype descriptions, imaging reports, and results of the behavioral assessments they have completed. The results of the present study will be submitted to peer-reviewed journals and/or reported at relevant conferences. Subjects will be able to withdraw from the study at any time without explanation. They will not suffer any penalty from the staff, nor will any repercussions be evident in their care due to this decision.

### Participants

Some investigators have noted that predictors of communication difficulties may differ for the subgroup of children with CP in early life (Pennington et al., 2020). Therefore, we will limit our study participants to those with BCP (associated with more serious complications and a more common prevalence of communication problems) (Geytenbeek et al., 2015) to find reliable prognostic markers for this population. Brain MRI-based classification systems have been widely recommended and used for classifying different types of brain lesions in children with CP, and different neuroimaging methods may reveal the different pathogenic patterns responsible for CP (Ditchfield, 2017; Himmelmann et al., 2017). Among all the types of lesions, PWMLs are the most common neuroimaging finding in this population (Himmelmann and Uvebrant, 2011; Coleman et al., 2016; Himmelmann et al., 2017), and the severity of PWMLs has been shown to be associated with the severity of communication impairment (Geytenbeek et al., 2015; Coleman et al., 2016; Choi et al., 2017). Thus, we will also constrain neuroimaging to children with BCP and PWMLs to reduce the heterogeneity within our study population.

#### Inclusion Criteria

Children meeting the following criteria will be considered for enrollment in this study: (I) confirmed diagnosis of BCP by pediatric neurologists (Novak et al., 2017), (II) age 6 months to 2 years at the time of recruitment, (III) PWMLs as described on the MRI imaging report, and (IV) willingness by participants and parents to participate in the study.

#### Exclusion Criteria

Children will be excluded if they have any one of the following criteria: (I) blindness, severe visual impairment or hearing impairment (given the requirements of some language assessment modules); (II) other diseases (i.e., hereditary disease, cancer, severe infectious disease, severe heart disease, or progressive central nervous system diseases); (III) MRI artifacts affecting any further image processing analysis; (IV) insufficient cooperation to participate in the communication assessment; and (VI) a primary language other than Chinese among the family members.

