#### Withdrawal Criteria

Subjects will be withdrawn from this study at the discretion of the researchers if there are safety concerns or if the children are unable to complete follow-up examinations.

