While the SLTs are conducting the on-site CFCS rating, a caregiver will be asked to read the CFCS-Chinese version and conduct a retrospective assessment of the child’s communication performance in daily life. Then, the caregiver will be asked to determine his or her child’s CFCS level by taking into account the communication performance status on site. If there are 2 caregivers in the field, the ratings will be made simultaneously without discussion, and the one who spends more time with the child will be marked as the first caregiver and the other one will be marked as the second caregiver. The SLT will explain the CFCS language but will not discuss the CFCS outcome with the parents. The final CFCS levels will be determined by professionals (SLTs) in close collaboration with parents. The CFCS has good reliability with high intraclass correlation coefficients across different language versions (Hidecker et al., 2011; Vander Zwart et al., 2016; Wang and Wei, 2017; Choi et al., 2018; Mutlu et al., 2018) and has been widely used in multiple CP registries (Coleman et al., 2015; Hustad et al., 2016; Mei et al., 2016; Vander Zwart et al., 2016; Wang and Wei, 2017; Mutlu et al., 2018) as a recommended, suitable tool for evaluating everyday communication in children with CP. The CFCS-Chinese version has also shown good reliability with intraclass correlation coefficients of 0.88 between an SLT and a caregiver and of 0.86 between the first and second caregivers for children with CP (Wang and Wei, 2017).

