
**TABLE 1 T1:** Descriptors for levels of the CFCS, FCCS, and VSS.

Level	CFCS	FCCS	VSS
I	Effective sender/receiver with familiar/unfamiliar partners	Effective communicator in most situations	No speech motor disorder indicated
II	Effective, but slower-paced sender and/or receiver with familiar and/or unfamiliar partners	Effective communicator in most situations but may need help	Speech motor disorder indicated but is usually understandable to unfamiliar listeners
III	Effective sender and receiver with familiar partners; not effective with unfamiliar partners	An effective communicator in some situations	Speech motor disorder indicated and is not typically understandable to unfamiliar listeners out of context
IV	Inconsistent sender and/or receiver with familiar partners; not effective with unfamiliar partners	Assistance required in most situations, especially with unfamiliar partners	No understandable speech
V	Seldom effective sender/receiver with familiar partners; not effective with unfamiliar partners	Communicates unintentionally using movements and behavior	–

*CFCS, Communication Function Classification System; FCCS, Functional Communication Classification System; VSS, Viking Speech Scale.*

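### Exclusion (IV) and the follow-up withdrawal rule can remove children from the primary CFCS outcome because they cannot engage with the assessment, and non-returners get no CFCS rating

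*Protocol article*

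**What the plan says.** Three provisions of the protocol article bear on who ends up with a primary outcome.

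- Exclusion Criteria, item (IV): a child is excluded for "insufficient cooperation to participate in the communication assessment".
- Withdrawal Criteria: apart from safety concerns, researchers may withdraw children "if the children are unable to complete follow-up examinations".
- Study Procedures: for families who do not come back, the CSBS-DP questionnaire "will be collected by trained researchers during a telephone survey for participants who are reluctant to return to the hospital for follow-up". No CFCS rating is provided for in that call.

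On the outcome, Study Procedures says: "The primary outcome measure for this study is the communication function classification system (CFCS) rating". On timing: "At the age of 48–60 months, the participants will be invited back to the hospital for a follow-up assessment". Recruitment is at 6 months to 2 years (Inclusion Criteria).

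Primary Outcome Measures describes the CFCS as a therapist's rating built from questioning the parents, watching the child with the family, and play, with the level settled together with the parents. A caregiver also rates the child on site. For the Chinese version the article cites "intraclass correlation coefficients of 0.88 between an SLT and a caregiver". Table 1 defines level V as "Seldom effective sender/receiver with familiar partners; not effective with unfamiliar partners". For analysis, level I is unimpaired and levels II–V are impaired (Development and Validation of Prediction Models).

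**The concern.** A prediction study needs the outcome label for the whole population in which the tool will be used, and above all for the children whom the tool is meant to find. Here, two rules turn on whether a child can take part in or complete the follow-up assessment, and that ability is itself related to communication. If they are followed as written, children who could be rated on the CFCS, and who would probably count as impaired, may never enter the primary analysis.

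The 20% dropout allowance in Sample Size replaces numbers. It cannot correct a loss that depends on the outcome. The Discussion presents the sample as representative, and its limitations paragraph does not mention this selection. The telephone provision adds a second, separate loss: contact is made, but the primary outcome is not collected.

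**Working it through.** **1. The plan's own figures.** Sample Size gives f² = 0.10, 6 predictors, α = 0.05 and power 0.80. The overall F test in multiple regression (noncentrality f² × N, degrees of freedom 6 and N − 7) gives power 0.798 at N = 142 and 0.801 at N = 143, so the stated 143 is reproduced. With 20% dropout, 143 / 0.80 = 178.75; the plan states 178 (178 × 0.80 = 142.4), a trivial rounding difference. The sample-size arithmetic is not in dispute.

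**2. When can item (IV) act?** The only communication assessment described in the text is at 48–60 months.
- If (IV) is applied then, it is an exclusion after baseline on something related to the outcome.
- If it is applied at 6–24 months, it cannot establish whether the child will be assessable at four to five years, and it may still select on developmental severity.

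**3. Does the CFCS need the child's cooperation?** Largely not, given the three sources of the rating listed in Primary Outcome Measures. The tests that do need it are secondary. For the WPPSI-IV subtest, Secondary Outcome Measures names language impairment and reduced intellectual ability among the reasons for non-completion and provides a composite score as a fallback. No comparable fallback is given for the primary outcome.

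**4. Illustration of size.** Inputs from the document: total loss 20%; prevalence p = 47% (Sample Size; 62/131 = 47.3%) and 78% (upper end of the 46–78% range in the Introduction). Assumed, not in the document: impaired children are lost r times as often as unimpaired children.

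Loss in unimpaired children: q = 0.20 / (p·r + 1 − p). Observed prevalence: p(1 − r·q) / 0.80.

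| p | r | q | r·q | Observed prevalence |
|---|---|---|---|---|
| 0.47 | 1 | 0.200 | 0.200 | 47.0% |
| 0.47 | 2 | 0.20/1.47 = 0.136 | 0.272 | 42.8% |
| 0.47 | 3 | 0.20/1.94 = 0.103 | 0.309 | 40.6% |
| 0.78 | 1 | 0.200 | 0.200 | 78.0% |
| 0.78 | 2 | 0.20/1.78 = 0.112 | 0.225 | 75.6% |
| 0.78 | 3 | 0.20/2.56 = 0.078 | 0.234 | 74.6% |

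Bound, if every lost child were impaired: (0.47 − 0.20)/0.80 = 33.8%, and (0.78 − 0.20)/0.80 = 72.5%.

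In numbers at p = 0.47, of 142.4 children analysed, the impaired fall from 66.9 (r = 1) to 60.9 (r = 2) or 57.8 (r = 3). In a one-quarter test cohort that is 16.7, 15.2 or 14.4.

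**5. Effect on performance measures.** Overall accuracy depends on prevalence. AUC does not move with prevalence alone, but it can move if the severity mix within the impaired group changes. As a purely hypothetical example for sensitivity, suppose it is 0.90 in severe and 0.70 in milder impairment, and half of impaired children are severe. It is then 0.800 with no severe child lost, and (0.90 × 0.35 + 0.70 × 0.50)/0.85 = 0.782 with 30% of severe children lost. The documents give no basis for the actual size or direction.

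**The case against.** The case against is substantial on several points.

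- **Timing.** A reader might infer that (IV) can act only at follow-up. Study Procedures applies the criteria before entry, a baseline neurobehavioral assessment exists, and Figure 1 is not shown. The text supports an ambiguity, not a certainty. Both readings remain unsatisfactory, as shown above.
- **Level V.** Table 1 defines it by effectiveness and does not mention cooperation, and poor cooperation can be behavioural. That such children would be rated impaired is probable, not stated. The impaired class is wide, though (levels II–V).
- **Withdrawal.** It is discretionary, and nothing says that a CFCS rating already obtained is discarded. Details of missing-outcome handling may stand in a fuller document. But eligibility, withdrawal and what the telephone call collects are fixed in this article, and as written they permit the loss.
- **Non-returners.** A reader might infer that all three routes lose the outcome where impairment is likeliest. For families unwilling to return, nothing in the text links this to impairment; a link is plausible only.
- **Agreement of 0.88.** A reader might take this as support for telephone ratings. In this study the caregiver reads the form, has its language explained by the therapist, and takes the on-site performance into account. The figure is not shown to hold by telephone, and caregivers cannot be blinded to the child's history.
- **Magnitude.** The loss ratios are assumed. The 47% comes from a general cerebral palsy sample, while Participants says communication problems are more common in bilateral disease. Near 78% the shift is only about 2–3 points.

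**Conclusion.** The point holds in a limited form and should be acted on. Item (IV) and the withdrawal rule can remove children because they cannot engage with an assessment that the primary outcome does not strictly require, and these children would probably be classed as impaired. Independently, families reached only by telephone lose the primary outcome, whether or not that loss is informative. The planned allowance is about 35 children (178 × 0.20 = 35.6), but it covers dropout from all causes and does not estimate how many are affected by either route.

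The likely result is a milder case mix, so that accuracy, and possibly AUC, may not represent the target population. The actual size is unknown. The illustrated shifts (47% to about 41–43%; 78% to about 75–76%) rest on a 20% total loss and an assumed two- to threefold excess loss in impaired children. The documents do not support the stronger claims that outcome-dependent loss is certain or that it arises through all three routes.

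**What to change.** - State that item (IV) and non-completion of follow-up examinations apply only to the performance tests (PPTV-R, WPPSI-IV), and that neither bars a CFCS rating or inclusion in the primary analysis. Withdrawal for safety is not affected.
- Rate the CFCS for every child who attends, from caregiver interview and observation.
- Retain every child with a CFCS rating, and record the reason for any test not completed.
- Add a caregiver-rated Chinese CFCS to the telephone call already planned for non-returners. Flag these ratings and run a sensitivity analysis that excludes them.

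The cost is a short amendment and a few minutes per call. The downside is that telephone ratings lack the therapist's on-site observation and blinding, and their agreement with the on-site rating is unknown; the flag and sensitivity analysis address this only in part. The article reports that recruitment is under way, so the change is best made before the 48–60-month visits: labels not collected then cannot be recovered by analysis.
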